## Abstract

**Background:**

Anxiety disorders are among the most prevalent mental health concerns affecting children and adolescents. Despite their high prevalence, statistics indicate that fewer than 25% of individuals in this demographic seek professional assistance for their condition. Consequently, there is a pressing need to develop innovative interventions aimed at improving treatment accessibility.

**Objectives:**

This study aims to assess the effectiveness of Internet-delivered Cognitive Behavioral Therapy (iCBT) for adolescents with anxiety, with a specific emphasis on involving parents in the treatment process.

**Methods:**

The study is structured as a parallel three-armed randomized controlled trial, comparing Internet-delivered Cognitive Behavioral Therapy (iCBT) with planned feedback, iCBT with on-demand feedback, and a waitlist control group, each group including 56 participants. Participants in the two iCBT conditions will undergo a 14-week treatment regimen, while those in the waitlist control group will wait for 14 weeks before starting iCBT with planned feedback. Additionally, participants in the iCBT groups will be randomly assigned to receive a booster session or not. The study design is factorial including two factors: type of therapist feedback (factor 1) and booster or no booster (factor 2). The study population comprises adolescents aged between 12 and 17 years, residing in Denmark, diagnosed with an anxiety disorder according to DSM-5 criteria. The primary outcome measures are the Youth Online Diagnostic Assessment and the Spence Children’s Anxiety Scale. Assessments will occur at baseline, post-treatment, and at 3-, 6-, and 12-month follow-ups post-treatment.

**Discussion:**

The findings of this study are anticipated to contribute to improving the accessibility of evidence-based treatments for adolescents with anxiety.

**Trial registration:**

The study is registered at clinicalTrials.gov, under protocol ID 22/59602. The Initial release was the 16.10.2023, first posted due to technical problems 16.04.2024. https://clinicaltrials.gov/study/NCT06368557?locStr=Odense,%20Denmark&country=Denmark&city=Odense&page=2&rank=13.

**Supplementary Information:**

The online version contains supplementary material available at 10.1186/s13063-024-08511-0.

## Administrative information

Note: the numbers in curly brackets in this protocol refer to SPIRIT checklist item numbers. The order of the items has been modified to group similar items (see http://www.equator-network.org/reporting-guidelines/spirit-2013-statement-defining-standard-protocol-items-for-clinical-trials/).

## Introduction

### Background and rationale {6a}

Anxiety disorders are the most prevalent mental health issues among children and adolescents [1, 2], affecting approximately 5–12% of youth in western countries [3, 4]. Research indicates a significant increase in anxiety disorder prevalence during the transition from childhood to adolescence [5]. Left untreated, anxiety disorders frequently become chronic or recurring, persisting into adulthood [6, 7].

Cognitive behavioral therapy (CBT) is an effective treatment for anxiety in young individual [8], recommended as the primary treatment option according to NICE guidelines [9]. Despite the availability of effective treatments and the potential long-term consequences of untreated anxiety disorders, less than 25% of affected youth seek professional help [10, 11] with even fewer receiving evidence-based treatment [12].

Common barriers preventing adolescents from seeking treatment include social stigma, shyness and fear of peer rejection [13–17], as well as preference for self-reliance [13, 17, 18]. Additionally concerns about confidentiality, privacy and anonymity [13, 14, 19], worries concerning treatment costs, transportation or waiting times [14, 20], and limited access to psychological services [13, 14, 21] are common barriers. Addressing these barriers is crucial for developing interventions that will enhance treatment accessibility.

Internet-based cognitive behavioral therapy (iCBT) presents a promising alternative to traditional face-to-face treatment, offering greater flexibility, autonomy, cost-effectiveness, and convenience [22]. Several randomized controlled trials (RCTs) have investigated the efficacy of iCBT programs for children and adolescents with anxiety disorders with promising results, including significant reductions in symptom severity [23–36]. Furthermore, a recent meta-analysis showed that Internet-based treatment is effective in reducing anxiety in youth when compared to both active and inactive control groups [37]. This trial seeks to examine the effectiveness of a newly developed iCBT program, CoolMinds, with the aim of facilitating its integration into routine care for adolescents in Denmark.

### Objectives {7}

The primary aim of the study is to examine the effectiveness of CoolMinds, an Internet-delivered cognitive behavioral therapy intervention, among adolescents aged 12–17 years. Specifically, the study seeks to examine the effectiveness of CoolMinds when administered with either planned feedback or on-demand feedback from a therapist, compared to a waitlist control group. Furthermore, the study will explore the effectiveness of delivering one booster session compared to no booster session in enhancing treatment outcomes.

We hypothesize that a higher proportion of participants in the two treatment conditions will achieve recovery from their primary anxiety diagnosis compared to those in the waitlist control group. Additionally, both treatment conditions are hypothesized to result in greater reduction in anxiety symptoms compared to the waitlist control group. We also hypothesize that the booster session will increase and better maintain reduction in anxiety symptoms over time.

### Trial design {8}

The study is a randomized controlled trial (RCT) designed as a superiority trial with three parallel conditions: (1) iCBT with planned feedback, (2) iCBT with on-demand feedback and (3) waitlist control. The allocation ratio is 1:1:1 for each condition. The participants will be stratified by age into age groups 12–14 years and 15–17 years respectively to secure an even age distribution across conditions. Additionally, all active participants will be randomized to receive a booster session 10 weeks after end of treatment. The randomization will take part 10 weeks into treatment with an allocation ratio of 1:1. The design of the randomized trial is thus factorial including two factors: type of therapist feedback (factor 1) and booster or no booster (factor 2). Data will be collected using parent and adolescent questionnaires at five time points: pre-treatment, post-treatment and at follow-ups after 3, 6 and 12 months post-treatment. Participants in the waitlist condition will no longer take part in the study after the post waitlist measures, but will be offered iCBT with planned feedback after completing the waitlist period (Fig. 1).

**Fig. 1 Fig1:**
[figure not shown]
Participant flow diagram

## Methods: participants, interventions and outcomes

### Study setting {9}

The study will be conducted at the Centre for Digital Psychiatry (CEDIP), an online clinic and research facility at the psychiatric hospital in the Region of Southern Denmark, as well as Center for Psychological Treatment of Children and Adolescents (CEBU), a research and teaching center at Aarhus university, Denmark. All data will be collected from these two centers in Denmark.

### Eligibility criteria {10}

*Inclusion criteria:* Participants must be (1) between 12 and 17 years of age (both included) and have (2) a principal anxiety diagnosis according to DSM-5 criteria, as assessed by a clinical psychologist, (3) the ability to read and write Danish, (4) Internet access, and (5) a parent (or other legal guardian) able to participate in treatment alongside the adolescent. *Exclusion criteria:* (1) diagnosed with an autism spectrum disorder, (2) an Attention Deficit Hyperactive Disorder (ADHD/ADD), (3) psychotic symptoms, (4) bipolar disorder, (5) current suicidal ideation or self-mutilating behavior, (6) current alcohol or substance abuse, (7) a moderate to severe depression (8) current eating disorder and (9) received CBT for an anxiety disorder within the past 12 months.

The eligibility criteria for clinicians performing the intervention are as follows: must have a master’s degree in clinical psychology, and be employed at either Centre for Digital Psychiatry or Center for Psychological Treatment of Children and Adolescents.

### Who will take informed consent? {26a}

The research team will obtain online and oral informed consent from both the legal guardians and the participants between 15 and 17 years. If participants reach the age of majority (18 years old) during the trial, independent consent will be obtained. For participants between 12 and 14 years, online and oral informed consent will be obtained from their legal guardians.

All potential participants will be invited to a mandatory video call, where they will be informed about the study. Along with the invitation, will they receive written participant information, which they are encouraged to read before the call. During the video call, participants will have the opportunity to provide oral consent, or take time to reflect. If they choose to reflect, they can give oral consent by contacting the research staff within 1 week form the call. Once oral consent is obtained, participants will be asked to complete an online consent form. This consent will be collected using REDCap, a secure web platform for building and managing online databases and surveys [38, 39].

## Interventions

### Explanation for the choice of comparators {6b}

The use of a waitlist control is deemed necessary to investigate the effectiveness of the iCBT treatment compared to no treatment. In some of the most recent RCTs of iCBT for adolescents with anxiety disorders utilizing a waitlist control group, participants in this group also experienced an improvement in anxiety symptoms despite not receiving the intervention immediately [30, 32, 35].

Ambiguous results regarding the effect of dose and type of clinical support during iCBT treatment, coupled with a significant proportion of adolescents not fully responding to treatment, underscore the necessity for further research.

Research on adult iCBT programs suggests that even minimal therapist contact is sufficient to establish an adequate alliance [40, 41]. Interventions with lower degrees of guidance, such as automated support or on-demand support, have produced effect sizes comparable to interventions with higher levels of therapist guidance [42]. Similarly, within research on adolescent iCBT programs, the therapeutic alliance is evaluated as good even in iCBT formats with little to no therapist support [43]. Berg, Rozental [23] found no significant differences in treatment outcomes when iCBT was delivered with weekly feedback or weekly feedback with additional chat sessions. This suggests that only a limited amount of therapist support may be sufficient to obtain treatment effect, mirroring results from the research on adults.

### Intervention description {11a}

The Internet-based program, CoolMinds, is based on cognitive behavioral therapy for adolescents following the work by Kendall [44] and further developed by, e.g., Rapee, Lyneham [45] and Cunningham, Rapee [22]. The iCBT is delivered through online treatment modules, allowing adolescents to progress through the program at their own pace. The main treatment components include psychoeducation, cognitive restructuring, exposure therapy, and relapse prevention. The program comprises eleven sessions for adolescents and ten sessions for parents to be completed simultaneously over a 14-week period, including a booster session to be completed 10 to 12 weeks after end of treatment. The adolescent program and the parent program do not interact and are separate programs. See Tables 1 and 2 for an overview of the program content.

**Table 1 Tab1:** Adolescent program content

Session		Content
1	Introduction	Welcome to the program. How to use the program and its functions.
2	Psychoeducation (specific)	Completing self-report measures on anxiety to obtain baseline functioning. Psychoeducation about specific anxiety disorders of choice: *social anxiety disorder, separation anxiety disorder, generalized anxiety disorder, panic disorder, specific phobias, OCD.*
3	Psychoeducation (general)	What is anxiety and what causes it? How many people experience anxiety?
4	Realistic thinking	Identification of problem situations. Identifying and challenging unrealistic thoughts.
5	Goalsetting and rewards	Setting goals and working towards them. Using rewards to maintain motivation.
6	Exposure 1	Creating an exposure hierarchy. Planning and executing exposure tasks. Reducing safety behavior.
7	Exposure 2	Creating an exposure hierarchy. Planning and executing exposure tasks. Reducing safety behavior.
7a	Exposure for OCD	Disorder specific content regarding exposure tasks and safety behavior.
7b	Exposure for panic disorder	Disorder specific content regarding exposure tasks and safety behavior.
8	Behavioral experiments	Planning and executing behavioral experiments and more challenging experiments.
9	The toolbox	Specific strategies to use when experiencing anxiety or difficulties with exposure, e.g., calm breathing, problem solving, constructive feedback.
10	Relapse prevention	Skills overview and maintenance. The journey of overcoming anxiety. Self-assessment of current challenges. What do I do if my anxiety returns or if I need more help?
11	What now?	Reward for completion. How to stay motivated and continue work.
12	Booster	Refreshing treatment techniques.

**Table 2 Tab2:** Parent program content

Session		Content
1	Introduction	Welcome to the program. How to use the program and its functions.
2	Psychoeducation	What is my adolescent going through? Psychoeducation about specific anxiety disorders of choice: *social anxiety disorder, separation anxiety disorder, generalized anxiety disorder, panic disorder, specific phobias, OCD.* What is anxiety and what causes it? How many people experience anxiety?
3	Parent traps	Parental behavior. How anxious am I?
4	Do it yourself! Realistic thoughts	What will my child work with during the program? Trying out realistic thinking yourself (e.g., heights, water, spiders).
5	Do it yourself! Goals and rewards	What will my child work with during the program? Trying out goalsetting and rewards yourself.
6	Do it yourself! Exposure	What will my child work with during the program? Trying out exposure tasks yourself (e.g., heights, water, spiders).
7	School	How to handle school absenteeism due to anxiety. Helping the adolescent cope with anxiety in school. Includes an informal print-out to be handed out to, e.g., teachers.
8	Relapse prevention	The journey of overcoming anxiety. How to support the adolescent during difficulties.
9	Need more help	Where can I seek more help for my own potential difficulties? Where can I as a parent seek more help for my adolescent?
10	What now?	How to continue supporting the adolescent.
11	Booster	Refreshing treatment techniques.

#### iCBT with planned feedback

Participants in the planned feedback iCBT condition will receive written feedback from their therapist on assignments every week. They will also have the opportunity to contact their assigned therapist through messages via a built-in text module within the program and receive asynchronous support if needed.

#### iCBT with on-demand feedback

Participants in the on-demand feedback iCBT condition will not receive any planned contact with the therapist. However, they will have the option to contact the therapist through messages within the program and receive asynchronous support.

In both treatment conditions, the therapist may spend a maximum of 15 min giving feedback per week. While we have advised therapists to adhere to this standard time used per participant in The Internet psychiatry, we cannot fully ensure adherence to this rule as it is up to the discretion of each therapist. Since there is no evidence on what amount of therapist support is sufficient for adolescents, the allowed time spent giving feedback will not differ between the two conditions. Participant depression and suicidality will also be continuously monitored in both intervention conditions using in-session questionnaires (see section “Plans for assessment and collection of outcomes {18a}”).

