#### Waitlist

Participants in the waitlist condition will be instructed to wait for 14 weeks. After this waiting period, they will no longer take part in the study, but will be offered iCBT treatment with planned therapist feedback. If participants do not wish to receive the iCBT treatment, they will receive assistance in finding another relevant treatment if needed.

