#### Weekly outcomes

The 8-item Children’s Anxiety Scale (CAS-8) [61]. The CAS-8 is a short version of the SCAS containing 8 items. I has shown acceptable psychometric properties, with good reliability [61].

The Short Mood and Feelings questionnaire (S-MFQ) [62]. The S-MFQ is a short version of MFQ, at shows high accuracy for discriminating MDD cases from non-cases [63].

Sociodemographic measures will be gathered on parents regarding age, level of education, job status, civil status, gender, and primary caregiver in case of single parents. For the adolescents, information will be gathered regarding age and gender.

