### Participant timeline {13}

All participants will need to register through a website to participate in the project. During registration, participants will be required to complete an initial screening questionnaire to assess exclusion criteria. If an exclusion criterion is met, the participant will automatically be informed within the questionnaire that they are unable to participate and will be given the choice to either continue or discontinue their application process.

Participants who complete the screening questionnaire and who are not excluded are invited to participate in a video call with one of the research staff members, during which they will receive information about the study, their rights, and a consent form. Participants will have the option to verbally consent to participation during the video call, or they may be prompted to schedule another time to clarify their participation.

Participants who provide both written and verbal consent will receive an online questionnaire package. For adolescents, this package will include the following assessments: The Youth Online Diagnostic Assessment (YODA), Spence Children’s Anxiety Scale (SCAS), Child Anxiety Life Interference Scale (CALIS), The Mood and Feelings Questionnaire (MFQ), and EuroQol-5 Dimension Youth (EQ-5D-5L). For parents, the package will include the caregiver version of YODA, SCAS-C/P, MFQ, and CALIS.

After completing the questionnaires, participants will be invited to a video call with a clinical psychologist for an assessment interview. Based on the collected data and the assessment interview, the clinical psychologist will determine if the participant meets the diagnostic criteria for an anxiety diagnosis according to DSM-5, and are eligible to take part in the study. If eligible, the participant will be randomized in to the three conditions. If the participants are in the two treatment conditions they will be provided with login credentials for the treatment platform. If the participants are in the waitlist, the will be notified that they will get the login credentials after answering the post-waitlist questionnaires.

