## Assignment of interventions: Blinding

### Who will be blinded {17a}

Given the nature of the study examining the effectiveness of a novel format of psychotherapy and the examination of difference in therapist support, blinding participants and clinicians is not possible. Additionally, the research team actively engages in day-to-day project operations, including the screening for suicidality, and therefore, the research team is not blinded.

However, to mitigate bias, the trial results will be analyzed using pseudo-anonymized data. This means that only the ID numbers will appear on the data sheet, aiming to achieve as close to assessor blinding as possible within the research design.

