### Interim analyses {21b}

The data monitoring committee will conduct monthly analyses to ensure that there are no significant harms related to participating in this project. The members of the data monitoring committee will all have access to these interim analyses. Termination of the trial will be decided in unison, but in case of disagreement, the final decision lies with the primary investigator.

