### Methods for additional analyses (e.g., subgroup analyses) {20b}

A large number of additional analyses will be conducted. Logistic regression will be used to analyze associations between treatment arms and the secondary outcome YODA (dichotomized) at 3-month follow-up post treatment as well as each of the 20 NEQ items at post-treatment. Linear mixed model regression will be used to analyze associations between treatment arms and the following outcomes through all time points from pre-treatment to 12-month follow-up post treatment: SCAS-C score, CALIS, MFQ score by adolescent, SCAS-P, CALIS, MFQ score by parent, EQ-5D-5L score, CSQ-8 score, and SUS score. Furthermore, linear mixed model regression will be used to analyze associations between treatment arms and WAI-SF at treatment sessions 2, 4, 6, 8, and 10 and at post treatment, and between treatment arms and weekly measures of CAS-8 and S-MFQ. Linear regression will be used to analyze associations between treatment arms and WAI-TECH-SF and engagement at post-treatment, as well as the cost-effectiveness analysis.

Finally, we wish to conduct a post hoc exploratory growth mixture model that can provide trajectories of change in symptoms through the trial across the different sessions and post-measurements.

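### The safety rule speaks of discontinuing worsening adolescents from the study, which conflicts with the commitment to keep assessing every enrolled participant

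*Protocol article*

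**What the plan says.** **Stopping for safety.** Section {11b} sets a stepped rule. If depressive symptoms rise above the clinical cutoff or suicidal ideation appears, the clinician contacts the adolescent and guardians to talk over whether the adolescent should leave the study. Up to three such contacts are allowed. At a third episode during treatment, the purpose of the contact is to take the participant out of the study and help find other care if needed.

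**Keeping participants in assessment.** Section {18b} describes persistent inactivity as a reason to discontinue the treatment, not the study. It then sends the post-treatment and follow-up measures to everyone enrolled unless they decline, expressly including those who do not complete treatment. Sections {11d} and {20c} commit to intention to treat.

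**Who is monitored.** In the description of the on-demand arm, depression and suicidality are "continuously monitored in both intervention conditions using in-session questionnaires". The waitlist is different: "Participants in the waitlist condition will be instructed to wait for 14 weeks", and its members are told that "they will get the login credentials after answering the post-waitlist questionnaires". Other places name no arm: the weekly outcomes section lists the S-MFQ, the blinding section refers to "the research team actively engages in day-to-day project operations, including the screening for suicidality", the interim analyses section promises "monthly analyses to ensure that there are no significant harms related to participating in this project", and the harms section {22} has a committee oversee S-MFQ and CAS-8 screening. Section {20b} plans comparisons "between treatment arms and weekly measures of CAS-8 and S-MFQ" without saying whether the waitlist is one of those arms.

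**The concern.** Leaving the treatment and leaving the study are different acts. The first costs nothing in the analysis if outcomes are still collected. The second removes the post-treatment SCAS, and here the reason for removal is that the participant got worse. The protocol uses one wording for inactivity and the other for worsening, so staff could reasonably think that two different actions are meant.

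The primary analysis compares pre-to-post SCAS change between conditions in a linear mixed model. A participant taken out before week 14 would contribute a baseline SCAS only. Maximum likelihood handles missing outcomes well when the reason for missingness is captured by the data in the model. Here the reason is recorded on other measures, and nothing in the article puts those into the primary model.

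The monitoring text bears on this. If safety screening ran only in the iCBT arms, exits of this kind would arise only there, and removing participants who worsened would tend to flatter iCBT. Whether screening is confined in that way is not stated.

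**Working it through.** **The rules side by side**

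| Section | Trigger | Action | Outcomes afterwards |
|---|---|---|---|
| {11b}, first contacts | Depression above cutoff, or suicidal ideation | Discuss leaving the study | Not stated there |
| {11b}, third episode | Same, during treatment | Leave the study | Not stated there |
| {18b} | Persistent inactivity | Leave the treatment | Collected unless declined |
| {18b}, general | Any enrolled participant | – | Collected unless declined |
| {11d}, {20c} | – | – | Intention-to-treat analysis |

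Section {18b} attaches its commitment to enrolment and gives non-completion of treatment as its example. Someone formally taken out of the study could be read as outside it. An intention-to-treat commitment keeps the participant in the analysis set but does not supply an outcome that was never collected. The conflict is therefore not fully settled by the other sections.

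**Figures that bear on it**

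1. Sample size section: 134 needed, 20% attrition. 134 / 0.80 = 167.5, rounded up to 168, which matches the plan. 168 / 3 = 56 per arm, which also matches.
2. Attrition allowance: 168 − 134 = 34, and 34 / 168 = 20.2%. Each safety exit treated as a study exit uses one of these 34.
3. Bias: the document gives no rate of such exits and no SCAS difference between those removed and those retained. If a fraction *f* of the iCBT participants is lost, and their mean change is *g* points worse than that of those retained, a complete-case mean shifts by *f* × *g*. With purely assumed values, *f* = 0.02 and *g* = 5 give 0.1 point; *f* = 0.10 and *g* = 15 give 1.5 points. The design difference is 10 points. This illustrates the mechanism and is not an estimate: the trigger is depression or suicidality, not SCAS, and the illustration assumes no comparable loss on the waitlist.

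**Monitoring by arm**

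In-session forms need the platform, and the waitlist has no login until after its post-waitlist questionnaires, so that channel cannot reach 56 of 168 adolescents (33.3%). But {18a} says that questionnaire measures are collected in REDCap, which does not depend on the login. The harms section restricts screening to no arm. The term used in {20b} cannot settle the matter: the same section applies it to outcomes up to 12 months, yet "Participants in the waitlist condition will no longer take part in the study after the post waitlist measures". Table 3, where a waitlist schedule could appear, is not shown.

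**The case against.** The strongest defence is that {11b} is headed as being about allocated interventions, that the early contacts only discuss stopping, and that {18b} already promises all measures to non-completers. With the intention-to-treat commitment, this makes treatment discontinuation the likely intention. That stands as a reading of intent. It does not remove the wording, which appears twice in the one section staff would consult when a participant worsens, and which differs from the wording that {18b} uses for inactivity.

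A reader might infer something stronger: that the waitlist goes unscreened for depression and suicidality for 14 weeks. The documents do not support this. The sentence naming the two iCBT arms closes a paragraph that compares those two arms and does not exclude the third. The weekly outcomes and harms sections name no arm, REDCap offers a route, and the schedule table is not shown. What is left is that waitlist screening is not stated.

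A reader might also infer a known bias in favour of iCBT. That would need {11b} to be followed literally despite {18b}, and screening to be confined to the iCBT arms. Neither is established.

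**Conclusion.** The inconsistency is real and rests on text that can be read: {11b} against {18b}, {11d} and {20c}. Taken literally, {11b} would produce missing primary outcomes caused by worsening. Treatment discontinuation was probably meant, so this is a wording fault with a possible consequence for the primary comparison, not a demonstrated loss of data. No size of bias can be derived from the document. The only firm figure is that each such exit would use one of 34 allowed losses. Entry excludes moderate to severe depression and current suicidal ideation, and no rate of later worsening is given, so no number of cases is claimed.

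The monitoring sentence calls for clarification only. Non-anxiety care is unrestricted in all arms, so the open question is detection, not access to help.

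**What to change.** **Main change.** At both mentions in {11b}, replace discontinuation from the study with discontinuation from the allocated treatment (or waiting period). Add that post-treatment and follow-up outcomes are still collected as scheduled for that arm unless the participant declines. For the waitlist, that means the post-waitlist measures. This costs nothing and changes no clinical threshold or action.

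**Clarification.** Confirm that the committee screening in {22} covers the waitlist through REDCap. If so, reword the monitoring sentence in the on-demand section to name all three arms, and define in {20b} which arms the weekly comparisons include. This too is a wording change.

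If no waitlist screening proves to be scheduled, adding it is a separate decision with a trade-off, because repeated questionnaires may affect a comparator meant to represent no treatment. As a guide to effort, the S-MFQ at weeks 4, 8 and 12 would be 3 × 56 = 168 forms, plus committee review and call-backs.
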